### Study aims

This early-stage effectiveness-implementation hybrid study has two primary aims:

Aim 1. To develop mNavigator by adapting an open-source digital health case management platform, CommCare, to incorporate protocol-driven treatment for pediatric cancer.

Aim 2. To evaluate the effectiveness of mNavigator for improving provider compliance with protocol-driven treatment for pediatric cancer and reducing treatment abandonment.

A secondary aim of the study is to understand factors that facilitate or inhibit the implementation of mNavigator in tertiary care settings for pediatric cancer.

### Study setting

The study will be implemented at Bugando Medical Centre (BMC) in Mwanza, Tanzania. BMC serves a catchment area of 15 million people and is one of three tertiary cancer centers in Tanzania that treat pediatric cancer patients. In 2019, the oncology unit at BMC comprises 2 medical oncologists, 1 radiation oncologist, 1 junior medical officer, 10 nurses, 2 pediatric patient navigators, and 1 clinic coordinator. Annually, approximately 150 new pediatric patients are diagnosed with cancer at BMC. The Tanzanian Ministry of Health Community Development, Gender, Elderly and Children collaborated with representatives from each of the three tertiary pediatric cancer centers in Tanzania to develop a protocol–treatment consensus for two of the most common national pediatric cancer diagnoses -- Burkitt lymphoma (BL) and retinoblastoma (Rb). These diagnoses constitute 35% of children with cancer presenting to BMC. Despite the introduction of these guidelines, provider compliance with these guidelines is less than 20%. ([name], Personal communication).

### Intervention

#### Materials

Materials specific to intervention development are described below.
Treatment protocols: International pediatric cancer consortiums have developed resource-adapted treatment protocols specifically for use in LMICs [19–22]. The study uses resource-adapted treatment protocols for Burkitt lymphoma and retinoblastoma, which have already been approved for use at three pediatric cancer centers by the Tanzanian Ministry of Health Community Development, Gender, Elderly and Children [23].Software and subscription plan: mNavigator will be developed using CommCare, a highly validated, HIPAA-compliant, open-source digital health platform developed by Dimagi Inc. [24, 25] This extensible and modular platform includes an existing module for tracking individuals through a continuum of service delivery that can be customized for the proposed application to manage pediatric cancer care [26]. The CommCare platform has two core components: a mobile application and CommCareHQ. CommCare mobile application runs on a mobile phone or tablet, and is built on a decision and logic-processing platform that can support oncology providers and staff by providing critical data-quality checks based on patient data and calculations at each point of service throughout treatment. CommCareHQ is a cloud-based system, which allows application development, data management and reporting. The application builder enables complex branching logic and data validation suitable for the implementation of a standardized protocol. The application works offline, making its use highly feasible in settings with low connectivity. Access to the CommCare platform is via a subscription plan with tiered pricing. For this study, the Pro plan was purchased ($500/month).Training: All study staff participating in the development of mNavigator completed two online training modules on the Dimagi Academy website (CommCare fundamentals and CommCare application building) prior to accessing CommCare HQ.CommCare accounts: Each study staff member created an account to log in to CommCare HQ. Account creation and access controls are managed centrally by an admin user.Hardware: mNavigator will be deployed on Android tablets. For this study, mNavigator was deployed on Samsung Galaxy Tab. A devices. Since the system is hosted on Dimagi’s servers and included in the subscription service, additional hardware related to data storage was not needed for this study or for future routine clinical use.

A list of resources is described in Additional file 1 Table S3. Resources are described as existing (available irrespective of study status) or study-supported (potentially not sustainable post-study).

#### Intervention components

mNavigator comprises four key modules:
Pre-diagnosis module: This includes data entry forms that enable registration of new patients, collection of socio-demographic data and clinical history, entry of laboratory and imaging results at presentation, and assignment of a working diagnosis.Burkitt lymphoma (BL) module: This includes data entry forms specific to patients diagnosed with Burkitt lymphoma to document cancer staging, planned treatment (including details of the dose and timing of for each chemotherapy cycle), end of therapy evaluation, and follow up visit planning. Throughout the forms in this module, Burkitt lymphoma treatment guidelines are incorporated as prompts for data entry, computation of relevant lab values, adjustment of chemotherapy regimen, scheduling of chemotherapy cycles, and post-treatment follow up.Retinoblastoma (Rb) module: This module is similar to the Burkitt module, except that it is specific to patients diagnosed with retinoblastoma and incorporates the specific treatment guidelines for retinoblastoma.Non-BL/Rb module: This module includes data entry forms for patients who are not diagnosed with Burkitt lymphoma or retinoblastoma. The forms do not track the treatment of the patients or incorporate treatment guidelines. Rather, they enable tracking of patient demographics and outcomes.

#### Intervention users

Four users (1 junior physician, 2 patient navigators, and 1 clinic coordinator) will be trained to use mNavigator at BMC. In addition to the physician, one patient navigator has medical training as a clinical officer. The remaining two users have training in social work. All four have worked in the oncology department for at least 2 years and were chosen as the intended users of mNavigators since they are currently responsible for coordinating clinical care for pediatric cancer patients at BMC, and hence, frequently interact with patients and their families at the hospital. They are comfortable with smartphone technology (they own and use personal smartphones) and, as part of current job responsibilities, are knowledgeable with accessing online databases in cloud based systems.

#### Mode of delivery

The users will access mNavigator on an Android tablet (Samsung Galaxy Tab. A). To access mNavigator, users will log into the CommCare application then select mNavigator from a menu of applications. CommCare supports offline log in and data collection.

#### Intervention delivery

The users will use mNavigator during one-on-one interactions with patients and their caregivers. At the first interaction with each cancer patient, the users will register the patient. During subsequent interactions, users will:
Enter pre-diagnostic labs and imaging tests.Assign patients based on physician preliminary clinical evaluation to BL, Rb, or non-BL/Rb cohorts for further assessment.Complete and review pre-treatment staging and laboratory checklists for patients with preliminary Rb or BL diagnosis to facilitate protocol compliance.Deliver cancer educational information in video format.Review treatment guidelines with decision support algorithms to facilitate care coordination between mNavigator users and prescribing physicians.Enter information on changes in treatment plan, including referrals to outside hospitals, second line treatment, or palliation.Follow-up with patients to record health related outcomes (on treatment, off therapy, relapsed disease, etc.) and vital status.

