### Sample size and recruitment

Sample size estimates are based on the patient volume at BMC. Based on prior experience, approximately 150 new pediatric patients present each year for cancer management at BMC. Of these, approximately 50 patients are anticipated to have a diagnosis of BL or Rb. All new patients will be registered in mNavigator, and all patients with BL and Rb who provide informed consent will be tracked in the system for treatment management. Historical data is anticipated to be available for approximately 200 BL and Rb patients from 2015 to 2019 (i.e., 50 records/year). All available historical data will be used in the comparator arm. Similarly, approximately 15 health professionals at BMC are identified as individuals directly or indirectly impacted by mNavigator, all of whom will be approached for study participation. All prospective participants will be approached in person to provide study information and invite participation.

To ensure thematic saturation of qualitative data and that diverse perspectives are heard, we will complete an interview with parents of at least 12 BL and 12 Rb patients. Interviews may be recorded using an encrypted digital device.

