### Outcome measures

Study outcomes are summarized in Tables 3 and 4. Measurement of study outcomes is guided by the RE-AIM framework. In mNavigator, we will collect data points that will allow us to measure outcomes in the following domains:
Reach – e.g., proportion of eligible patients for whom protocol was used.Effectiveness – e.g., proportion of cases that abandoned care, with treatment completion and time from hospital presentation to confirmed diagnosisAdoption – e.g., proportion of providers who use the protocol, provider acceptability and satisfaction with mNavigator content, ease of delivery and credibilityImplementation/Compliance – e.g., proportion of protocol steps completed per patientMaintenance (measured in future studies)

**Table 3 Tab3:** Summary of outcomes related to intervention effectiveness and their measurement

Outcome	Measure	Data source
Change in protocol compliance (primary outcome)	Percent difference in protocol compliance with mNavigator and historical compliance. Protocol compliance is calculated as proportion of protocol steps completed, based on a compliance checklist.	mNavigator data from prospectively registered pediatric cancer patients from July 2019 – July 2020 and data extracted from paper charts for patients registered at BMC from 2015 – June 2019 entered into mNavigator
Change in treatment abandonment (secondary outcome)	Calculated as the difference in proportion of patients registered in mNavigator who abandoned treatment compared to historical controls who abandoned treatment. Treatment abandonment is defined as missing four or more consecutive weeks of treatment or follow-up while still on therapy.	Data from mNavigator (outcome form)
Change in treatment completion rate	Calculated as the proportion of patients registered in mNavigator who completed treatment compared to historical controls	Data from mNavigator (outcome form)
Change in time to diagnosis	Change in the number of days to diagnosis using mNavigator compared to historical controls. Time to diagnosis is computed as the duration from registration to diagnosis	Data from mNavigator (registration form; diagnosis form)

**Table 4 Tab4:** System-level outcomes related to the mNavigator application

Outcome	Measure	Data source
Usability^a^	System usability scale score ranging from 0 to 100. A SUS score above a 68 is considered above average and anything below 68 is below average.	10-point validated system usability scale

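### Death on treatment is recorded but not compared, and the abandonment rule leaves referrals and unrecorded historical deaths open, so the abandonment difference can shift without any change in abandonment

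*Protocol article*

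**What the plan says.** Under Intervention delivery, the Protocol article has mNavigator users "Follow-up with patients to record health related outcomes (on treatment, off therapy, relapsed disease, etc.) and vital status". They also "Enter information on changes in treatment plan, including referrals to outside hospitals, second line treatment, or palliation". Death, referral and change of plan are therefore meant to be captured for prospective patients.

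Table 3 (Outcome measures) lists four compared effectiveness outcomes: protocol compliance (primary), treatment abandonment (secondary), treatment completion and time to diagnosis. Death is not one of them, and it appears neither in the effectiveness examples above the table nor in the Quantitative analysis plan.

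The abandonment rule reads: "Treatment abandonment is defined as missing four or more consecutive weeks of treatment or follow-up while still on therapy". The measure is "Calculated as the difference in proportion of patients registered in mNavigator who abandoned treatment compared to historical controls who abandoned treatment". Completion is "Calculated as the proportion of patients registered in mNavigator who completed treatment compared to historical controls".

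Under Quantitative data collection, historical patients' data are abstracted from paper records into mNavigator, to the extent that the records hold them.

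Abandonment is not a side issue. Aim 2, one of the two primary aims, is "To evaluate the effectiveness of mNavigator for improving provider compliance with protocol-driven treatment for pediatric cancer and reducing treatment abandonment".

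**The concern.** A child can stop attending because the family abandons treatment, because the child has died, because care has moved to another hospital, or because the plan has changed. Table 3 gives a rule for the first and no stated rule for telling it from the others. Two consequences follow.

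- **Unequal recording.** Prospective patients are followed for vital status and referral. Historical patients have only what the chart shows. A historical child who died at home or was sent elsewhere, with nothing written down, looks like a child who missed four weeks. The same event in the prospective cohort would be recorded for what it was. Abandonment would then appear to fall under mNavigator with no change in families' behaviour.
- **Death as a competing event.** The denominator is all registered patients. A child who dies early can no longer abandon but stays in the denominator, so more deaths mean a lower abandonment proportion even if every death is correctly recorded.

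At stake is the credibility of an Aim 2 result, and whether a reader can tell fewer abandonments from more deaths.

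**Working it through.** **Inputs from the Protocol article.** Under Sample size and recruitment, "approximately 50 patients are anticipated to have a diagnosis of BL or Rb" in the prospective year, and about 200 historical records are expected at 50 per year. The historical figure reproduces: 50 × 4 = 200. One prospective patient is 1/50 = 2 percentage points; one historical patient is 1/200 = 0.5 points. The article gives no death rate, abandonment rate or misclassification rate, so every rate below is an assumption.

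**Model.** Let q be the abandonment risk among children who do not die first, d the proportion who die on treatment, and m the share of deaths counted as abandonment. Observed abandonment = q(1 − d) + m·d.

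**Step 1: unequal recording, same true experience.** Take q = 0.30 and d = 0.20 in both cohorts, with half of historical deaths unrecognised (m = 0.5) and none prospectively (m = 0).
- Historical: 0.30 × 0.80 + 0.5 × 0.20 = 0.24 + 0.10 = 34%.
- Prospective: 0.30 × 0.80 = 24%.
- Spurious fall: 10 points.

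With equal q and d the difference is simply m·d. Deaths of 10% give 0.5 × 0.10 = 5 points (32% vs 27%), and deaths of 30% give 0.5 × 0.30 = 15 points (36% vs 21%). If one in ten prospective deaths is also miscounted (m = 0.1, d = 0.20), the comparison is 34% vs 26%, an 8-point fall. The same arithmetic applies to unrecorded referrals.

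**Step 2: more deaths, perfect recording (m = 0), q unchanged at 0.30.**
- d = 0.10: 0.30 × 0.90 = 27%.
- d = 0.20: 0.30 × 0.80 = 24%, a fall of 3 points.
- d = 0.30: 0.30 × 0.70 = 21%, a fall of 6 points.

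Over q = 0.2 to 0.4 and the same rises in d, the fall is 2 to 8 points.

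A constant-hazard competing-risk model agrees in direction. With a = −ln(0.7) and h = −ln(0.9) or −ln(0.75), cumulative abandonment is a/(a + h) × (1 − exp(−(a + h))). This gives 28.6% and 26.3%, a fall of 2.3 points when death in the absence of abandonment rises from 10% to 25%.

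**Step 3: does completion reveal it?** In the model just used, the share neither dying nor abandoning falls from 0.7 × 0.9 = 63.0% to 0.7 × 0.75 = 52.5%, or 10.5 points. Completion would therefore drop visibly if nothing else changed. If abandonment also falls, it need not:
- Historical: abandonment 30%, death 10%, completion 100 − 30 − 10 = 60%.
- Prospective: abandonment 20%, death 20%, completion 100 − 20 − 20 = 60%.

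Table 3 would then show 10 points less abandonment and unchanged completion, with a doubling of deaths not displayed.

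**Step 4: precision.** At 30% abandonment in both cohorts, the standard error of the difference is √(0.21/50 + 0.21/200) = 0.072, about 7 points. For a comparison of deaths at 200 vs 50 (two-sided 0.05, assumed), power is about 50% for 10% vs 20% and about 91% for 10% vs 30%. The 95% interval half-width for 10% vs 20% is about 12 points.

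**The case against.** The case for leaving Table 3 alone has real force.

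- **The definition already excludes known deaths on a natural reading.** A child who has died is not still on therapy, and vital status, referral and palliation are recorded as distinct items. This stands. A reader might infer that the plan counts every death as abandonment, or cannot separate the two. The documents do not support that: the prospective data would allow separation, and what is absent is a stated rule for referrals and for deaths nobody recorded.
- **Completion is compared and would usually fall if deaths rose.** This also stands, and Step 3 shows the fall can be larger than the abandonment shift. A reader might infer that a harm signal would be invisible; that goes too far. But completion does not name death as the cause and can stay flat when fewer abandonments offset more deaths, so it is only a partial safeguard.
- **The competing-event shift is small.** A 2 to 3 point shift is well under one standard error of about 7 points. That is fair for Step 2. The recording difference in Step 1 can be larger, and it runs in one direction, towards mNavigator.
- **The article is condensed.** Form coding may well be set out elsewhere. But the list of compared outcomes and the abandonment definition are both stated in Table 3, so they can be judged as they stand. Absence of safety monitoring cannot be inferred from the article, and is not inferred here.
- **Historical death status may be incomplete.** True. It limits the death comparison, and it is also why an unknown category is needed.

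**Conclusion.** The point holds as a cheap, worthwhile improvement and not as a fatal flaw. Death on treatment is recorded but not compared. The abandonment rule implies that known deaths are excluded, but it does not deal with referred children still on therapy or with deaths missing from historical charts. Since the two cohorts differ in how well these events can be recognised, the abandonment difference may partly reflect record-keeping, in mNavigator's favour. A real rise in deaths can also lower abandonment, and completion does not always expose it.

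The size cannot be fixed from the documents. Under the assumed rates it is about 2 to 8 points when deaths rise from 10% to 20% or 30%, and about 5 to 15 points when half of historical deaths are taken for abandonment at death rates of 10% to 30%. Both ranges depend wholly on those assumptions.

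**What to change.** 1. In both cohorts, assign each BL/Rb patient one mutually exclusive end-of-treatment status: completed; died on treatment; abandoned; referred or change of plan recorded; still on treatment; unknown.
2. State in Table 3 that abandonment counts only absence not explained by a recorded death, referral or change of plan.
3. Add death on treatment to Table 3 as a compared outcome, reported for both cohorts beside abandonment and completion.
4. Add a sensitivity analysis that reclassifies the unknown patients, for example all as abandoned and then none, so that the reader sees how far the abandonment difference depends on missing historical information.

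**Cost.** A few lines in Table 3 and one tabulation, using items already collected prospectively and whatever the charts hold. Nothing in patient care changes. The downsides are a wide interval for death with about 50 prospective patients (power about 50% for 10% vs 20%, assumed) and possibly incomplete historical death status. The death comparison should therefore be presented as descriptive, with its interval and the number of unknowns in each cohort.

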### Theoretical framework for intervention development and evaluation

Our intervention development is guided by the Consolidated Framework for Implementation Research (CFIR) and our evaluation is informed by CFIR and RE-AIM [27, 28]. This study will address characteristics of the:
Outer setting (e.g., patients’ needs and resources, diagnosis delays, test availability);Inner setting (e.g., compatibility of the protocols with the existing workflows at BMC, organizational readiness to change),Individuals (e.g., providers’ self-efficacy for using the protocols, acceptability of intervention), andIntervention (e.g., using evidence-based protocols; low complexity of intervention design) in this project.

Details of how the study will address the characteristics listed above are presented in Additional file 1 Table S4.

### Study activities

Study activities are summarized in Table 2. The implementation process using CFIR comprises four iterative steps: Plan, Engage, Execute, Reflect and evaluate. As described below, these four iterative steps are incorporated throughout mNavigator development and evaluation.

**Table 2 Tab2:** Summary of study activities using the Consolidated Framework for Implementation Research process

CFIR phase	Activities	Tasks
PLAN	Workflow mapping	Existing clinical workflows Provider tasks Patient navigator tasks
	Form development	Translation of clinical workflows and national treatment guidelines to data entry forms Programming in CommCare HQ
ENGAGE	Quality assurance	Personas De-identified patient records Iterative testing and updates
	Usability testing	System usability score Think aloud method
EXECUTE	In-country training	Training on mNavigator In-country capacity building for sustainability
	Implementation in routine clinical use	Supported launch Full launch
REFLECT AND EVALUATE	Implementation- effectiveness hybrid design	Clinical effectiveness System evaluation Implementation factors

**Fig. 2 Fig2:**
[figure not shown]
mNavigator user interface draft. **a**. mNavigator home screen. **b**. List of forms built in for Burkitt lymphoma patients. **c**. Example case detail showing contact information of a fictitious patient. **d**. Example of data entry question on tumor staging with pictorial support. **e**. Illustration of automated calculation of next chemotherapy cycle dates. **h**. Display example of chemotherapy cycle status

#### Activity 3

*Program Quality Assurance:* A quality assurance plan was implemented to check mNavigator for comprehensiveness of patient scenarios and clinical workflows, accuracy of clinical recommendations, and alignment with treatment guidelines. Steps in the quality assurance plan included:
Development of fictitious personas to simulate patients and most common workflow pathways, and test programmed decision logic. Details of personas included socio-demographic characteristics, clinical history, cancer diagnosis and staging, and treatment plan.Testing the app for errors in flow or output using personas. Details of the personas were entered into mNavigator to assess the application flow, as well as to assess if calculations and recommendations being made are correct based on the standardized treatment protocol. An example of a correct application flow was for mNavigator to assign a patient to the Burkitt lymphoma module when a diagnosis of Burkitt lymphoma was entered in the diagnosis form. Any errors or areas for improvement were documented as detailed notes or checklists and used to inform revisions.Testing the app for errors in flow or output using historical patient data. mNavigator was further evaluated using historical patient data to assess the application flow, as well as to assess if calculations and recommendations being made are correct based on the standardized treatment protocol. Any errors or areas for improvement were documented as notes.

#### Activity 4

*Usability testing:* Research staff introduced approximately 15 BMC personnel to mNavigator during a study launch event in July 2019. Attendees were BMC health professionals who provide routine clinical care for pediatric cancer patients including patient navigators, clinical coordinators, health providers and other clinical staff as well as non-clinical staff and other key stakeholders whose buy-in was necessary for the successful implementation of mNavigator. One BMC staff member with database management and information technology skills was trained on how to further customize, deploy and manage mNavigator. A post-usability survey with the four mNavigator users was used to assess system usability (using the System Usability Scale), relative advantage over standard of care, acceptability and satisfaction. Additional feedback on system features received during the study launch was also documented as notes.

